### **B. Tentative titles of other Possible papers that can emerge from this research (not necessarily a part of the PhD- may be included if required)**

1. The effect of c-KMC on gut microbial composition in LBW infants in India.
2. Association between maternal postpartum depressive symptoms and stress on infant breast milk intake
3. Association between maternal postpartum depressive symptoms and stress on linear growth
4. Association between gut microbial composition of LBW neonates in which half have received c-KMC and their linear growth in the first six months of life.
5. Effect of c-KMC on neonatal skin condition in LBW infants
6. Association of maternal body composition with infant birth weight, breast milk intake and linear growth (from secondary data that will be generated from this work).

**Effect of community-initiated KMC on maternal postpartum depressive symptoms and stress - a randomized controlled trial**

**Introduction**

This plan of analysis is described for a randomised controlled trial conducted to evaluate the impact of community-initiated Kangaroo Mother Care (ciKMC) in low birth weight mother-infant dyads on maternal postpartum depressive symptoms and maternal salivary cortisol levels (a marker of stress). This document describes the methods of data analysis.

**Hypothesis tested**

Community-initiated Kangaroo mother care leads to reduction in the prevalence of postpartum moderate to severe depressive symptoms (prevalence ratio  $\leq 0.7$ ) and reduction in salivary cortisol levels (at least 0.3 SD in mean values) as a marker of maternal stress.

**Objectives**

To estimate the effect of community initiated Kangaroo mother care during the neonatal period in LBW infants on

- prevalence of moderate to severe postpartum depressive symptoms (Patient Health Questionnaire-9 score  $\geq 10$ ) and
- stress (measured by salivary cortisol levels) at the end of the neonatal period

**Outcomes**

- Primary: Prevalence of moderate to severe maternal depressive symptoms (PHQ-9 score  $\geq 10$ )
- Secondary:
  - Mean salivary cortisol levels (in ug/dl)
  - Prevalence of Mild depressive symptoms (PHQ-9 score 5-9)
  - Proportion of mothers reporting suicidal ideation
  - Mean Patient Health Questionnaire-9 (PHQ-9) scores

**Definition of postpartum depression**

As per DSM-IV/V (Am Asso. of Psy.) an episode of depression is specified as having a postpartum onset if it occurs *within the first 4 weeks* after delivery (American Psychiatric Association) with the argument that onset of such an episode with onset later than 4 weeks could not easily be identified as being related to childbirth.

**Validity of the PHQ-9 tool used in the study**

- PHQ-9 is a screening tool that has been previously validated against DSM IV criteria (gold standard) to diagnose Post-partum depression (PPD) and is found to be highly specific.

**Effect of community-initiated KMC on maternal postpartum depressive symptoms and stress - a randomized controlled trial**

- Gjerdingen D et al in 2009 in a study in 506 mothers demonstrated that the *sensitivity and specificity* of a PHQ-9 score  $\geq 10$  to diagnose major depression as compared to DSM IV criteria is 75% and 91%, respectively, for diagnosing PPD within 1 month of child birth. In another study by Arroll et al (2010) in 2642 participants where the sensitivity and specificity of a PHQ-9 score  $\geq 10$  to diagnose major depression as compared to DSM IV criteria was 74% and 91% respectively.
- Given that the tool used is a screening tool we have opted to use the term “depressive symptoms”. The categorizations of minimal, mild, moderate to severe are according to previous literature (Kronke et al, 2001). Minimal, Mild and Moderate to severe depressive symptoms are defined by PHQ-9 scores 0 to 4, 5 to 9 and  $\geq 10$ , respectively

**Process for PHQ-9 assessments**

- **Tool:** Validated PHQ 9 questionnaire (hindi version). This was the same hindi form that was pre-tested and used in one of our previous studies.
- **Process:** Assessment was done at home by an independent team at the *end of neonatal period* i.e. day 28 (window period was +7 days) (Though the workers are part of the intervention delivery team, it was ensured that the workers assessed PHQ9 in mothers belonging to a different area (PHC) where they were not involved in intervention delivery so that the observations are independent.) If door was locked or the mother was unavailable and her date of availability was uncertain, she / family was contacted either by home visit or phone for at least 3 times within the window period.
- **Training:** Workers were trained to conduct interview for PHQ 9 and fill the PHQ 9 questionnaire following the KMC-GCC form filling guidelines. The workers were reassessed and retrained by a faculty of the department of clinical psychology of AIIMS, New Delhi. The PI, Coordinators were also trained for assessing PHQ 9. Training logs are maintained.
- **Quality checks:** The PI of the study conducted random visits in 1-2% of the PHQ 9 assessments and checked whether the PHQ 9 scores matched when scored independently. Also around 2% of the interviews are being recorded after taking consent for recording.
- **Advise for consultation:** All Mothers, irrespective of any group, who are having scores  $\geq 10$  were advised to consult a nearby physician at the earliest for further advise. A standard message is given to the family. Facilitation was done wherever possible.

**Sample Size:**

**Effect of community-initiated KMC on maternal postpartum depressive symptoms and stress - a randomized controlled trial**

1950 mothers (975 in each group) was enrolled which was calculated to be sufficient to detect a 30% relative reduction in the prevalence of moderate to severe postpartum depressive symptoms (PHQ 9  $\geq 10$ ), assuming a baseline prevalence of 19%, and considering attrition of 10%

A subsample i.e. 550 mothers were enrolled for saliva collection to measure salivary cortisol levels (biomarker of stress). This was calculated to be sufficient to detect to detect a 0.3 SD i.e. 1.5 ug/dl decrease in the mean saliva cortisol levels considering attrition of 15%. 2 Saliva samples were collected in the morning before 12.00 hours before and after breastfeeding.

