Breastfeeding performance will be assessed using the validated IBFAT breastfeeding assessment tool (40) which is based on 4 parameters i.e. readiness to feed, rooting, fixing (latch on) and sucking. Higher score denotes better breastfeeding. Lactation failure, perceived breast milk insufficiency and use of breast milk substitutes during the neonatal period (enrolment to day 28) will be assessed by interviewing mothers with a semi-structured questionnaire on day 29 adapted from WHO/UNICEF resource material on breastfeeding counseling and UNICEF breastfeeding assessment tools (<https://www.unicef.org.uk/babyfriendly/baby-friendly->

[resources/guidance-for-health-professionals/tools-and-forms-for-health-professionals/breastfeeding-assessment-tools/](#)).

Assessment of depressive symptoms in mothers will be done at the end of the neonatal period i.e. day 28 of life, by the trained OM team using the validated PHQ-9 questionnaire which is also pre-tested (19). For maternal salivary cortisol determination which is being used as an indicator of stress, fasting salivary samples will be collected by placing cotton swab in the oral cavity of the mother in the morning around 7-8 am when the baby is 28 days old. The morning salivary sample at 7- 8 am is seen to correlate with the entire area under curve of the awakening response of cortisol and even a single sample per participant could assess whether a mother had lower or higher concentration of cortisol (44). As the cortisol levels may also vary in relation to breastfeeding (45), we will collect two salivary samples from each mother and baby in the morning (around 8 am) before and after breastfeeding when the baby is 28days old. The time of salivary sample collection and previous breastfeeding will be noted. The samples will be aliquoted, labeled and transported in cold boxes to the storage facility at CRL-SAS, Devli within around 8 hours where it will be stored in -20 °C in freezers until further analysis. Analysis will be done in CRL-SAS using quantitative ELISAs. The kits will be validated in our lab prior to testing of study samples. We also plan to collect saliva samples from the infant at day 28 as an exploratory exercise to study relationship of infant stress with maternal stress and its association with milk intake, though it is not a part of our primary objectives.

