# Stress (Salivary cortisol levels)

## Sample Size considerations

|                                                                                               |            |
|-----------------------------------------------------------------------------------------------|------------|
| Standard deviation of Cortisol in control mothers(ug /dl)                                     | 5          |
| Expected Mean difference (ug/dl) in Cortisol levels(~20%)
[mean in control mothers 7ug/dl] | 1.5        |
| Effect size (SD)                                                                              | 0.3        |
| Alpha error (%)                                                                               | 5          |
| Power (1- beta) %                                                                             | 90         |
| Required sample size per group                                                                | 234        |
| Total sample size required                                                                    | 468        |
| TOTAL SAMPLE SIZE APPROVED FOR THE STUDY (including attrition)                         | 550 |

Ref: Morelius E, Ortenstrand A, Theodorsson E, Frostell A. A randomised trial of continuous skin-to skin contact after preterm birth and the effects on salivary cortisol, parental stress, depression, and breastfeeding. Early human development. 2015;91(1):63-70.

9/3/2017

24

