**Effect of community-initiated KMC on maternal postpartum depressive symptoms and stress - a randomized controlled trial**

To examine effect of ciKMC on maternal moderate to severe depressive symptoms multivariable logistic regression analysis or analyses with generalized linear models of the binomial family with a log link shall be done. Additionally, multinomial logistic regression analysis will be done to examine effect of ciKMC on prevalence of categories of maternal depressive symptoms viz. minimal (reference group), mild, and moderate to severe depressive symptoms.

For estimating effect of ciKMC on continuous outcomes i.e. maternal salivary cortisol concentration and mean PHQ-9 scores multivariable linear regression will be done if distribution is normal. If distributions are skewed, appropriate transformation (log or others) will be done before conducting linear regression. Alternatively, we will use non-parametric tests such as Wilcoxon rank-sum test for comparison of these outcomes between study arms.

For all the analyses, univariable regression analysis will be done as an initial step to assess the effect of ciKMC on the outcomes considered. This will be followed by multivariable regression analysis after including potential confounding variables in the model, defined as variables which are unequally distributed between the two groups (relative difference of >10%).

Potential interaction between KMC and other variables will be examined by including interaction terms in the multivariable regression models. Stratified analysis will be presented and any biologic interaction will be estimated with the relative excess risk due to interaction (RERI).

Planned Sub-group analysis:

- 1) By preterm vs. term birth
- 2) Birth weight +/- 2 kg if it does not substantially correlate with term vs. preterm birth.

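### The SAP does not say which of the two saliva samples is the cortisol endpoint, and it gives recorded clock time no role although the stated sampling window is wider than the protocol's

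*Combined protocol and SAP*

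**What the plan says.** **Protocol, Description of the PhD sub-study (outcome ascertainment).** Fasting maternal saliva is to be taken "in the morning around 7-8 am when the baby is 28 days old". The reason given is that a 7-8 am value tracks the awakening response, so that even one sample can separate mothers with higher and lower cortisol. The protocol then says cortisol may vary with breastfeeding, and for that reason plans two samples around 8 am, one before and one after a feed. It adds: "The time of salivary sample collection and previous breastfeeding will be noted".

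**SAP, Sample Size.** Collection is reported as "2 Saliva samples were collected in the morning before 12.00 hours before and after breastfeeding". Fasting is not mentioned. The target is restated as "0.3 SD i.e. 1.5 ug/dl decrease in the mean saliva cortisol levels considering attrition of 15" per cent, the same SD and difference as in protocol Annexure 3.

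**SAP, Outcomes.** Cortisol is a secondary outcome, described only as a mean level in ug/dl. The protocol's Outcomes section lists it among the primary outcomes.

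**SAP, Plan of Analysis.** For "maternal salivary cortisol concentration and mean PHQ-9 scores multivariable linear regression will be done if distribution is normal". Skewed data are to be transformed, or the arms compared by a Wilcoxon rank-sum test. Adjustment is for variables whose relative difference between arms exceeds 10%. Collection time, fasting and time since feed are not named anywhere in the SAP's analysis.

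**The concern.** Two things are left open.

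1. **Which value is analysed.** Each mother gives two samples, and the protocol itself expects them to differ. The pre-feed value, the post-feed value and their average all fit the SAP's wording. A choice made after the results are seen raises the false-positive rate.

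2. **What happens to time of day.** The protocol's reason for its window applies to samples taken at 7-8 am; it does not cover later ones. If collection spread towards noon, any time-of-day variation adds to the residual SD unless it is modelled. The protocol plans to record the variable that would remove it, but the SAP gives that variable no role. The target of 1.5 ug/dl is set against an SD of 5 that was not revisited when the stated window changed.

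**Working it through.** **Inputs.** Protocol Annexure 3, salivary cortisol table: "Standard deviation of Cortisol in control mothers(ug /dl") is 5; the difference is 1.5 ug/dl ("mean in control mothers 7ug/dl"); alpha 5%; power 90%; "Required sample size per group" 234, total 468, approved 550. No sampling time is attached to the SD. Sidedness is not stated for cortisol; two-sided is assumed because it reproduces the figure.

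**Step 1: the plan's own figure.**
n per arm = 2 × (1.960 + 1.282)² × 5² / 1.5² = 233.5, so 234; total 468.
With the SAP's 15% attrition: 468 / 0.85 = 550.6, against 550 stated. The figure reproduces.

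**Step 2: sensitivity to the SD.** Power = Φ(1.5/SD × √(n/2) − 1.96). The values above 5 are assumptions, because the documents give no SD for sampling up to noon.

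| SD (ug/dl) | 1.5 as a fraction of SD | Power, 234 per arm (after 15% attrition) | Power, 275 per arm (no attrition) |
|---|---|---|---|
| 5 | 0.300 | 90% | 94% |
| 5.5 | 0.273 | 84% | 89% |
| 6 | 0.250 | 77% | 83% |

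The largest SD that keeps 90% power is 5.005 at 234 per arm and 5.43 at 275. There is no headroom once the planned attrition has occurred.

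**Step 3: the opposite direction.** The average of two samples with correlation r has SD = 5 × √((1 + r)/2). For assumed r of 0.9, 0.7 and 0.5 this is 4.87, 4.61 and 4.33, and power at 234 per arm is 91%, 94% and 96%. If the single-sample SD were 5.5 and r were 0.7, the averaged SD would be 5.5 × √0.85 = 5.07 and power 89%.

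**Step 4: cost of an open choice of sample.** Let Z₁ and Z₂ be the null test statistics for the pre-feed and post-feed values, with correlation r. The statistic for the average is (Z₁ + Z₂)/√(2(1 + r)). By simulation, the chance that at least one of the three exceeds 1.96 in absolute value is about 7%, 9% and 10% for r of 0.9, 0.7 and 0.5, against a nominal 5%. This step needs no assumption about the SD. It also leaves out the further choice among raw, transformed and rank analyses.

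**The case against.** **The protocol already planned two samples.** This stands. The second sample is not an SAP change, and the protocol's reason for it (feeding) is sound. What neither document supplies is a rule for using the pair.

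**Mean in the SAP might signify the average of the two samples.** The text does not support this. The same list gives mean PHQ-9 scores, where there is one assessment per mother, so mean there is the group mean.

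**A reader might infer that cortisol is now underpowered.** The documents do not support that. Power for a standardised 0.3 SD effect is 90% at 234 per arm whatever the SD is. The SD of 5 comes with no sampling time; at 5/7 = 71% of the control mean it may already contain timing spread. Large increases are also hard to reach. Suppose SD 5 and mean 7 describe 7-8 am, sampling is uniform over 7-12, and the decline is linear at b per hour. Then SD² = 25 + b² × (5² − 1²)/12 = 25 + 2b². A mean falling to zero by noon gives b = 7/4.5 = 1.56 and SD 5.46, which is 84% power. On those assumptions the 77% row could not occur.

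**A reader might infer that sampling really ran to noon, or that timing biases the arm comparison.** The SAP's wording sets an outer limit; the actual spread is not reported. Bias would need collection times to differ by arm, which the documents neither show nor exclude.

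**A reader might infer that clock time is barred from the model.** It is not. The SAP's list of baseline variables is open-ended, and the 10% rule could admit clock time if it were examined and found imbalanced. The rule would still leave it out when the arms are balanced, which is when it serves precision.

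**Conclusion.** The point holds as a gap in specification. The stated sampling windows differ, fasting is dropped from the description, no rule says which sample is analysed, and clock time has no assured place in the model. The clearest consequence is the open choice of sample: a false-positive rate of about 7-10% in place of 5%, for assumed correlations of 0.9 to 0.5, if the most favourable of three summaries were reported.

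The power consequence is conditional. The sample size is correct as calculated; it is unsecured only that 1.5 ug/dl is still 0.3 SD. The range of 84% to 77% at 234 per arm, or 89% to 83% at 275, rests on assumed SDs of 5.5 and 6, and using both samples could offset it. The gain from adjusting for clock time cannot be sized, because the documents do not say how much of the variance it explains.

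Cortisol is secondary in the SAP, so this should be settled before the cortisol analysis but does not threaten the depressive-symptom result.

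**What to change.** 1. Reconcile the protocol's sub-study description with the SAP's Sample Size section on sampling window and fasting, and state what was done.
2. Prespecify one cortisol analysis: both samples in a linear mixed model, after the planned transformation if skewed, with a random effect for mother and fixed effects for arm, pre- or post-feed, and recorded clock time. Clock time enters whether or not it is imbalanced. The arm effect is the cortisol result.
3. Report collection time by arm. This also tests the working assumption that clock time reflects the visit and not the intervention.
4. Add two separate sensitivity analyses: pre-feed samples taken in the 7-8 am window only; and adjustment for time since last feed. The latter is measured after randomisation, and the intervention promotes breastfeeding, so adjusting for it in the main model could remove part of the intention-to-treat effect.

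The cost is SAP wording and a little more analysis. It needs no new data, provided collection times were recorded as the protocol planned; the SAP does not confirm that they were.

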**Plan of Analysis**

The analysis will be done using STATA version 14 (Stata Corporation, College Station, TX). All analysis will be performed on intent to treat basis.

Group wise comparison will be done for distribution of baseline features such as

- household characteristics (wealth quintile, religion, caste, type of family, number of family members)
- maternal and paternal characteristics (mother's age, mother's education, maternal occupation, father's age, father's education and occupation)
- birth related characteristics (place and type of delivery, birth order, parity) and
- infant characteristics (sex, birth weight, gestational age)

Proportion who initiated breastfeeding within 1 hour, exclusive breastfeeding, hospitalizations (at the 1 month visit) will also be presented by group.

Gestational age will be calculated from ultrasonography (USG) report, hospital records or maternal recall, whichever available, in the given order of preference. Proportion of women with available antenatal USG will be reported.

The distribution of the continuous outcomes such as (maternal salivary cortisol concentration, PHQ-9 scores) will be examined by using histogram and normal probability plot. Skewness and kurtosis coefficient will be measured. If skewness coefficient tends to zero and kurtosis coefficient tends to 3, distribution will be normal. For normal distribution, mean and standard deviation (SD) will be reported for quantitative variables. Median and interquartile range (IQR) will be reported for non-normal distribution. For non-normal continuous outcomes appropriate transformation (log or others) will be done before applying the tests of association or we will use non-parametric tests such as Wilcoxon rank-sum test will be performed for comparison between study arms.

The proportion of minimal, mild and moderate to severe depressive symptoms as defined by the PHQ-9 scores will be presented by group.

**Effect of community-initiated KMC on maternal postpartum depressive symptoms and stress - a randomized controlled trial**

To examine effect of ciKMC on maternal moderate to severe depressive symptoms multivariable logistic regression analysis or analyses with generalized linear models of the binomial family with a log link shall be done. Additionally, multinomial logistic regression analysis will be done to examine effect of ciKMC on prevalence of categories of maternal depressive symptoms viz. minimal (reference group), mild, and moderate to severe depressive symptoms.

For estimating effect of ciKMC on continuous outcomes i.e. maternal salivary cortisol concentration and mean PHQ-9 scores multivariable linear regression will be done if distribution is normal. If distributions are skewed, appropriate transformation (log or others) will be done before conducting linear regression. Alternatively, we will use non-parametric tests such as Wilcoxon rank-sum test for comparison of these outcomes between study arms.

For all the analyses, univariable regression analysis will be done as an initial step to assess the effect of ciKMC on the outcomes considered. This will be followed by multivariable regression analysis after including potential confounding variables in the model, defined as variables which are unequally distributed between the two groups (relative difference of >10%).

Potential interaction between KMC and other variables will be examined by including interaction terms in the multivariable regression models. Stratified analysis will be presented and any biologic interaction will be estimated with the relative excess risk due to interaction (RERI).

Planned Sub-group analysis:

- 1) By preterm vs. term birth
- 2) Birth weight +/- 2 kg if it does not substantially correlate with term vs. preterm birth.

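### The SAP's multinomial model is aimed at PHQ-9 category prevalences, but its coefficients compare each category with minimal; this leaves the secondary outcome of mild symptoms without a matching estimate

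*Combined protocol and SAP*

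**What the plan says.** The SAP's Outcomes section defines both outcomes as prevalences. The primary is "Prevalence of moderate to severe maternal depressive symptoms (PHQ-9 score" ≥10), and the secondary list includes "Prevalence of Mild depressive symptoms (PHQ-9 score 5-9"). The cut-points are given under the validity of the PHQ-9 tool: "Minimal, Mild and Moderate to severe depressive symptoms are defined by PHQ-9 scores 0 to 4, 5 to 9 and" ≥10.

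The analysis text then provides three things:

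- A binary model, named only for the primary category: "To examine effect of ciKMC on maternal moderate to severe depressive symptoms multivariable logistic regression analysis or analyses with generalized linear models". The second option there is log-binomial regression.
- An additional three-category model: "multinomial logistic regression analysis will be done to examine effect of ciKMC on prevalence of categories of maternal depressive symptoms viz. minimal (reference group"), with mild and moderate-to-severe as the other two levels.
- A description, in the Plan of Analysis: "The proportion of minimal, mild and moderate to severe depressive symptoms as defined by the PHQ-9 scores will be presented by group". No interval, test or effect measure is attached to it.

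The SAP does not say which quantity will be taken from the multinomial fit. The protocol's Data analysis section allows logistic or log-binomial regression for categorical outcomes where baseline differences need adjustment. Its list of examples does not include mild symptoms.

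**The concern.** With minimal as the reference, the arm coefficient for category j is the log of P(j)/P(minimal) under ciKMC minus the same log under control. Its null hypothesis is that this ratio is equal in the two arms. The stated target is the prevalence of category j, and its null is that P(j) is equal in the two arms. The two nulls part company whenever the intervention moves mothers into or out of minimal from the third category. A fall in PHQ-9 ≥10, which the trial hypothesises, can do exactly that.

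At stake is the between-arm result for mild symptoms. If the coefficient is read as an effect on mild prevalence, a paper could report fewer mild cases when the only change was fewer cases at ≥10.

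**Working it through.** **Inputs from the documents.** Control prevalence of PHQ-9 ≥10 is 0.19 (SAP, Sample Size: "assuming a baseline prevalence of 19"%). Under ciKMC it is 0.133, a 30% relative reduction (protocol Annexure 3). There are 975 per arm with about 10% attrition, and α is 5% with 90% power.

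**Assumptions.** Tests are two-sided, since sidedness is not stated for this outcome. 877 per arm are analysed (975 × 0.90 = 877.5). The calculation is unadjusted. Control mild prevalence is not in the documents, so it is varied over 20%, 30% and 40%.

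**1. The plan's own figure.** For two proportions without continuity correction, with mean p̄ = (0.19 + 0.133)/2 = 0.1615:

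n = [1.960·√(2·0.1615·0.8385) + 1.282·√(0.19·0.81 + 0.133·0.867)]² / 0.057² = 874 per arm.

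This matches Annexure 3. Dividing by 0.90 gives 972, close to the stated 975. The sample size is not in question.

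**2. Planned effect, mild prevalence unchanged.** Relative risk ratio (RRR) for mild = [P(mild)/P(minimal)] under ciKMC ÷ the same under control. SE of its log = √Σ 1/(877·p) over the four cells involved. Chance of p<0.05 = Φ(|z|−1.96) + Φ(−|z|−1.96).

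At control mild 30%, minimal is 1 − 0.30 − 0.19 = 0.51 under control and 1 − 0.30 − 0.133 = 0.567 under ciKMC:

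- RRR = (0.30/0.567)/(0.30/0.51) = 0.51/0.567 = 0.899; log = −0.106
- SE = √[(1/0.30 + 1/0.567 + 1/0.30 + 1/0.51)/877] = 0.109
- |z| = 0.973; chance of p<0.05 = 16%

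| Control mild | Minimal, control → ciKMC | RRR for mild (true prevalence ratio 1.00) | Chance of p<0.05 |
|---|---|---|---|
| 20% | 61% → 66.7% | 0.915 | 11% |
| 30% | 51% → 56.7% | 0.899 | 16% |
| 40% | 41% → 46.7% | 0.878 | 24% |

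A comparison of mild prevalence itself rejects in 5%, because that prevalence is equal in the two arms. A simulation of 20,000 trials at control mild 30% gave 16.4% for the coefficient.

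**3. No effect of ciKMC.** With 51%, 30% and 19% in both arms and 877 per arm, simulated rejection was 5.1% for the mild coefficient and 4.9% for ≥10. The coefficients keep their level.

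**4. Can the same fit supply the prevalences?** An example table was fitted with 447, 263 and 167 mothers (minimal, mild, ≥10) under control and 500, 210 and 167 under ciKMC. The ≥10 coefficient was −0.112 although 167 of 877 were affected in each arm. The predicted ≥10 prevalence was 19.0% in both arms, so the target is recoverable from the model.

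**5. What a comparison of mild prevalence does when mothers step down one level.** If the planned 5.7 points move from ≥10 to mild, mild rises from 30% to 35.7%. SE = √[(0.30·0.70 + 0.357·0.643)/877] = 0.0224 and z = 0.057/0.0224 = 2.55, so a significant increase in mild symptoms appears in about 72% of trials. For the same shift the coefficient gives RRR 0.357/0.30 = 1.19 (minimal stays at 51%) and is significant in about 37%.

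**The case against.** Much of the case on the other side stands.

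- **The primary outcome.** A reader might infer that the primary result is at risk. It is not: PHQ-9 ≥10 has its own binary model, and the multinomial model is introduced as additional. If mild fell by 30% relative with ≥10 fixed at 19%, the multinomial ≥10 coefficient would be significant in 12%, 25% and 51% of trials at control mild 20%, 30% and 40%. That pattern is not the SAP's hypothesis, and it concerns a category that is tested elsewhere.
- **Type I error.** A reader might infer that an inert intervention could be made to look effective. Step 3 shows otherwise.
- **The hypothesised ratio.** With mild fixed at 30%, a true prevalence ratio of 0.70 for ≥10 appears as an RRR of (0.133/0.567)/(0.19/0.51) = 0.63. Most of that gap is ordinary odds-ratio behaviour, since the binary odds ratio is (0.133/0.867)/(0.19/0.81) = 0.65.
- **Displayed proportions.** All three will be shown by group, so a careful reader could see that mild prevalence had not moved. This is a real safeguard, but it comes without an interval or a test.
- **Other cover for mild symptoms.** The protocol's general text could be read as allowing a binary model. It is conditional on baseline differences and does not name mild symptoms, so the cover is partial.
- **Reading of the output.** The SAP never says that RRRs will be reported as prevalence effects, and predicted prevalences are compatible with its text. That makes this a gap in specification; the model itself is valid.
- **The remedy.** Mild prevalence read alone can mislead as well, as step 5 shows.

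**Conclusion.** The point holds as a modest, inexpensive improvement. For the prevalence of mild symptoms, a listed secondary outcome, the only between-arm model named in the SAP has coefficients that do not estimate that prevalence. Under the trial's own design effect with mild unchanged, the mild coefficient is significant in about 11% to 24% of trials instead of 5%.

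The size rests on the assumed control mild prevalence of 20% to 40%, on 877 analysed per arm, and on a two-sided unadjusted test. The mismatch itself needs none of these, and covariate adjustment does not change what the coefficient measures. The consequence is that a real shift may be credited to the wrong category. The documents do not support a claim of inflated error under no effect, or of a threat to the primary conclusion.

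**What to change.** Keep the multinomial fit and state in the SAP what will be read from it:

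- the predicted prevalence of minimal, mild and moderate-to-severe symptoms in each arm, with the between-arm difference and ratio and a 95% CI for each;
- the joint 2-df test of the arm terms as the test of any shift across categories;
- that coefficients against minimal are not tests of category prevalence, and that inference on PHQ-9 ≥10 comes from the binary model.

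The three category differences should be presented and interpreted together, never mild alone, because mild prevalence rises when mothers improve from ≥10 to mild.

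The cost is a few sentences in the SAP and a standard post-estimation step in Stata (margins after mlogit). No new data are needed. The downside is the one in step 5: a rise in mild symptoms can reflect benefit, and the text must say so.
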